### Study outcomes

The primary efficacy end point is percentage of patients with any new stroke events (ischemic or hemorrhage), including fatal stroke, at 14 days.

Secondary outcome measures include,IPercentage of patients at 14 days and 90 days with new clinical vascular events (ischemic stroke/hemorrhagic stroke/TIA/myocardial infarction/vascular death) as a cluster and evaluated individually;IImRS score, dichotomized at percentage with score 0–2 versus score 3–6, at 14 days and 90 days follow-up;IIIChanges in NIHSS scores at 14 days and 90-days follow-up;IVEfficacy end point would also be analyzed stratified by etiologic subtypes (nonintracranial artery diseases versus intracranial artery diseases), by time randomization (<12 h versus ≥12 h), by qualifying event (TIA versus MIS), and by age (dichotomized at a 5-year cut point closest to median age).

Safety end points include,IModerate to severe bleeding event, according to the Global Utilization of Streptokinase and Tissue Plasminogen Activator for occluded Coronary Arteries definition, including fatal bleeding, intracranial hemorrhage and other hemorrhagic events required transfusion of blood, even causing hemodynamic compromise requiring intervention at 90 days;IITotal mortality at 14-days follow-up;IIIAdverse events/severe adverse events reported by the investigators in 14-days follow-up.

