**Fig. 1 Fig1:**
[figure not shown]
Study flowchart

Patients meeting these criteria and offering informed consent would be randomized into 2 arms:IReceiving a 100-mg dose of aspirin and placebo rivaroxabanIIReceiving a 10-mg dose of rivaroxaban and placebo aspirin

Patients would receive certain study medication from day 1 to day 14. The first dose would be given within 24 h of symptom onset. From day 15 to day 90, all patients would receive 100-mg dose of aspirin as standard antiplatelet therapy. Study visits would be performed on the day of randomization at day 14 and day 90. At randomization and during follow-up visits, the following information would be collected: a neurologic evaluation (mRS and NIHSS); a physical examination, including measurement of weight (kilogram) and vital signs (supine systolic and diastolic blood pressure, heart rate); laboratory tests, a neurological dysfunctions assessment, and concomitant medications and adverse events. For ensuring the safety of patients during the study, the trial should be stopped if the probability that rate of intracranial hemorrhage exceeded 5 % or the rate of other hemorrhagic events is more than 10 %. The progress of the study would be monitored by the data and safety monitoring board for ensuring the high standards of ethics and patient safety.

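### The only formal major-bleeding endpoint is at 90 days, although the arms differ only on days 1-14; all-cause death and adverse events are safety endpoints only to day 14

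*Protocol article*

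**What the plan says.** **Treatment periods (Study procedures, text after Figure 1).** "Patients would receive certain study medication from day 1 to day 14". Then: "From day 15 to day 90, all patients would receive 100-mg dose of aspirin as standard antiplatelet therapy".

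**Visits and data (same section).** "Study visits would be performed on the day of randomization at day 14 and day 90". The items collected at randomisation and at the follow-up visits include "laboratory tests, a neurological dysfunctions assessment, and concomitant medications and adverse events".

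**Safety endpoints (Study outcomes).** There are three, each with one window:
- GUSTO moderate-to-severe bleeding, including fatal, intracranial and transfused bleeds, ending "even causing hemodynamic compromise requiring intervention at 90 days";
- total mortality, at 14 days;
- adverse events and "severe adverse events reported by the investigators in 14-days follow-up".

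**Efficacy endpoints (Study outcomes).** The primary endpoint is any stroke, ischemic or hemorrhagic, at 14 days. The vascular-event composite, mRS 0-2 versus 3-6, and NIHSS change are each given at both 14 and 90 days. The composite covers ischemic stroke, hemorrhagic stroke, TIA, "myocardial infarction/vascular death) as a cluster and evaluated individually".

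**Objective (Study objective).** Whether rivaroxaban is safe is part of the primary objective.

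**The concern.** For an anticoagulant given for 14 days, the most direct safety question is how much major bleeding it causes while patients take it, set against the strokes it prevents in the same period. The plan measures the strokes at 14 days but gives its formal major-bleeding endpoint only a 90-day window, most of which is common treatment. Bleeds on common aspirin, if equally frequent in both arms, carry no information about the randomised contrast. They pull the ratio toward 1 and add noise, which makes a non-significant bleeding comparison more likely.

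The other two safety endpoints have the opposite limit. They stop when study drug stops, so a non-vascular death or a serious adverse event on, say, day 20 belongs to no dedicated safety endpoint, even though the patient is seen and asked about adverse events at day 90. Because safety is half of the primary objective, these windows bear on a headline conclusion.

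**Working it through.** **1. The plan's own figure.** The only sample-size figure concerns 14-day stroke (Statistical considerations). The stated arcsine formula is n = ½[(u_α + u_β)/(sin⁻¹√p1 − sin⁻¹√p2)]². With two-sided 5%, 90% power, p1 = 0.10 and p2 = 0.072 it gives 2,093.7 per group, against 2,095 stated, so it reproduces. Adding 5% gives 2,095 × 1.05 ≈ 2,200 per arm, 4,400 in total. This figure says nothing about bleeding; it only supplies the 2,200 per arm used below.

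**2. Share of common treatment.** Days 15 to 90 are 90 − 14 = 76 days, and 76/90 = 84%.

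**3. Windows side by side.**

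| Outcome | Day 14 | Day 90 |
|---|---|---|
| Any stroke, including hemorrhagic | primary | components in the secondary composite |
| Vascular composite, including hemorrhagic stroke and vascular death individually | yes | yes |
| mRS 3-6 | yes | yes |
| GUSTO moderate-to-severe bleeding | no | yes |
| Total mortality | yes | no |
| Adverse and serious adverse events | yes | no (but collected) |

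**4. Effect of the bleeding window (assumed rates, because the article gives none).** Power by the same arcsine approach is Φ(√(2n)·|sin⁻¹√p1 − sin⁻¹√p2| − 1.96), with n = 2,200 per arm and √(2n) = 66.33.

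| Assumed bleeding, rivaroxaban v aspirin | Risk difference | Relative risk | Power |
|---|---|---|---|
| 1.0% v 0.5% by day 14 | 0.5 points | 2.0 | 0.496 |
| plus 0.5% in each arm: 1.5% v 1.0% | 0.5 points | 1.5 | 0.323 |
| 0.4% v 0.2% by day 14 | 0.2 points | 2.0 | 0.233 |
| plus 0.3% in each arm: 0.7% v 0.5% | 0.2 points | 1.4 | 0.136 |

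**5. Sensitivity to the late rate.** Let the late risk be equal in both arms and proportional to the early aspirin risk r: either r × 76/14 (constant daily rate) or half of that. The 90-day risk is p14 + (1 − p14) × late risk. Aspirin-arm risks of 0.1%, 0.2% and 0.5% by day 14 were tried.
- A day-14 relative risk of 2 becomes about 1.15 (constant rate) or 1.27 (half rate).
- A day-14 relative risk of 3 becomes about 1.31 or 1.53-1.54.
- Worked case, 0.2% and relative risk 3: late risk = 0.002 × 76/14 = 0.01086. The 90-day risks are 0.01284 and 0.01679, a relative risk of 1.31. The risk difference is 0.396 points against 0.400 at day 14. Power (normal approximation for two proportions) falls from 56% to 19%, or to 28% at half the rate.
- With no late bleeding nothing changes.

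**6. What is left out after day 14.** From the table in step 3, late bleeding, hemorrhagic stroke, vascular death and poor mRS all have a 90-day count. What remains is non-vascular death, which enters at 90 days only as part of mRS 3-6, and adverse and serious adverse events on days 15-90.

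**The case against.** The strongest reply has four parts.

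- *The strategy is what is being tested.* The Discussion states the hypothesis as a 14-day rivaroxaban regimen followed by aspirin against aspirin alone, and all analyses are intention to treat. The 90-day ratio is then a correct estimate for that strategy, it captures bleeding after the switch, and the absolute excess is almost unchanged. This stands: 90 days is a legitimate window, and attenuation of the ratio is not bias in the estimate of that target. It does not supply the missing on-treatment comparison.
- *Early bleeding is partly covered.* Hemorrhagic stroke sits in the 14-day primary endpoint, and other bleeds may be reported among 14-day adverse events. This also stands, but neither is an analysis of the GUSTO endpoint, and major extracranial bleeding has no 14-day comparison of its own.
- *The size is assumed.* True. Only the direction is secure, and only if late bleeding is present and similar in both arms.
- *The article is condensed and its list need not be exhaustive.* Extra tables could sit in a fuller plan. But the article does state a window for each safety endpoint, and it writes two windows for each of the vascular events, mRS and NIHSS. The point concerns windows that are stated.

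A reader might go further and infer that late harm is not counted, or that benefit and harm never share a window. The article does not support either. Four kinds of harm are counted at 90 days (working, step 6). Vascular events and bleeding share the 90-day window; stroke, mortality and adverse events share the 14-day one.

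**Conclusion.** The point holds in a limited form. The primary efficacy endpoint is at 14 days, and the only formal moderate-to-severe bleeding endpoint is at 90 days, 84% of which is common aspirin. No on-treatment comparison of that endpoint is stated. If late bleeding is similar in the two arms, the relative risk and the power at 90 days understate what the randomised period would show. In the assumed example relative risk falls from 2.0 to 1.5 and power from about 50% to about 32%. The true size cannot be derived from the article, and in that example even the day-14 comparison has only moderate power. The absolute risk difference is essentially unaffected.

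Separately, 90-day all-cause mortality (in effect, non-vascular death) and day 15-90 serious adverse events have no dedicated safety endpoint, and the collection of adverse events at day 90 does not match an endpoint that stops at day 14. This is worth correcting because safety is part of the primary objective, but it does not invalidate the design. Which bleeding window should lead is open to argument; reporting both is not.

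**What to change.** In Study outcomes:
- Define GUSTO moderate-to-severe bleeding at day 14 (randomised-treatment period) and at day 90, with absolute differences and relative risks at each.
- Report total mortality and serious adverse events at day 14 and at day 90.
- Reconcile the adverse-event endpoint, now limited to 14 days, with Study procedures, which collects adverse events at the day-90 visit.

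The cost is endpoint wording and a few additional tables. Both visits are already scheduled and adverse events are already recorded at each; bleeding onset dates are needed to assign each event to its period. No change to sample size or treatment is involved.

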### Randomization, allocation concealment and blinding

Subject numbers would be assigned sequentially as each patient enters the study. After receiving an informed consent, patients fulfilling the inclusion criteria would be randomized by computer-generated random numbers (Microsoft Excel 2010, Redmond, WA, USA) at statistics research office, Fourth Military Medical University. A clinical research associate would make opaque blinded envelopes (with consecutive numbers) and deliver them to each participating center. Random allocation would be performed within 24 h after a patient enrolled. The block size and treatment-assignment table would not be available to the researchers until the end of the trial.

The study medication would be stored under the conditions specified on the label in a locked, safe area of the pharmacy department to prevent unauthorized access. Both the study medication and the placebo would be indistinguishable; they would be manufactured by the same company and similar in appearance, organoleptic characteristics, and presentation.

In the event of emergency, an investigator ([name]) and a clinical pharmacist ([name]) would decide whether it’s necessary to unblind the subject’s treatment assignment using the unblinding envelopes provided to the hospital. If unblinding was necessary, the investigator must record the reason for unblinding, as well as the date and time of the event. In each participating center, an independent researcher would be assigned to collect the trial paper and electronic records. In the central trial coordinating office, an independent research assistant ([name]) would have access to all unblinded data and maintain confidentiality of patient records.

### Statistical considerations

The primary null hypothesis of this trial is as follows: in patients with TIA or MIS treated with aspirin 100 mg per day, there would be no difference in 14-days risk of stroke (ischemic or hemorrhagic) in those treated with a 14-days regimen of rivaroxaban 10 mg per day, when therapy were initiated within 24 h of symptom onset.

The minimum necessary sample size in the trial is established by the requirement to detect the smallest expected clinically meaningful treatment difference comparing the treatment with placebo. According to the results of previous clinical studies [4, 5], we speculated the 14-day risk of stroke recurrence in the placebo (aspirin) group was about 10 % among TIA or MIS patients treated with aspirin within 24 h of symptom onset. The results from our preliminary study were used to calculate the sample size (unpublished data). A relative risk reduction of 28 % (relative risk with addition of rivaroxaban is 0.72) was the smallest difference we would attempt to detect. The following equation was used for calculating the sample size:$$ \mathrm{n}=\frac{1}{2}{\left(\frac{u_{\alpha }+{u}_{\beta }}{{ \sin}^{-1}\sqrt{p1}-{ \sin}^{-1}\sqrt{p2}}\right)}^2 $$

With a two-sided 5 % significance level (α) and a 90 % power (1-β), *p*1 of 0.10, *p*2 of 0.072, the minimal sample size per group was estimated to be 2095 patients. About 4400 participants in total 2 groups was a final estimated sample size with 5 % dropouts (medication nonadherence). Missing values would be remained missing, and patients would be censored at their last follow-up assessment (time of clinical event, end of study, or last visit before loss to follow-up).

All analyses would be intention to treat. In these analyses we would compare conventional-dose of rivaroxaban versus aspirin. Kaplan-Meier estimates of the cumulative risk of a stroke (ischemic or hemorrhagic) event during a 14 days’ follow-up, with hazard ratios and 95 % confidence intervals calculated using Cox proportional hazards methods and the log-rank test to evaluate the treatment effect would be reported. The Chi-square test of association would be used to compare groups at baseline as appropriate. Logistic regression would be used to determine the significance of the results obtained. All statistics would be two-sided with *p* <0.05 considered significant.

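### Two unranked routes to the primary result (Cox/log-rank and logistic regression) leave the deciding p-value and effect measure open

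*Protocol article*

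**What the plan says.** Study outcomes in the protocol article sets the endpoint as a proportion: "The primary efficacy end point is percentage of patients with any new stroke events (ischemic or hemorrhage), including fatal stroke, at 14 days". Statistical considerations frames the null hypothesis as a difference in 14-day risk and sizes the trial on two proportions, 0.10 and 0.072.

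The same section then gives two analyses. The first is Kaplan-Meier estimation of cumulative stroke risk over 14 days, together with a hazard ratio and its interval. Its wording on method is "calculated using Cox proportional hazards methods and the log-rank test to evaluate the treatment effect would be reported". The second comes two sentences later: "Logistic regression would be used to determine the significance of the results obtained". Between them stands "The Chi-square test of association would be used to compare groups at baseline as appropriate".

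The section also says that every analysis is by intention to treat, that missing values are left missing, and that patients are censored at the last follow-up assessment. It does not rank the two analyses, tie the logistic model to an endpoint or list covariates for either model.

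**The concern.** One sentence has the log-rank and Cox analysis evaluate the treatment effect. Another has logistic regression settle significance. Both are current text in the same paragraph, and nothing limits the second to secondary endpoints. In a confirmatory superiority trial a reader should know in advance which p-value decides and on which scale the effect will be stated. Here either could be chosen after the results are known.

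Two further points follow. The logistic model has no named covariates, so its adjustment set could be picked late, and baseline significance tests are a familiar prompt for doing so. An ordinary logistic model also needs a known 14-day status for each patient, and no rule is given for those lost earlier.

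**Working it through.** **Inputs from Statistical considerations.** p1 = 0.10, p2 = 0.072 (relative risk 0.72), two-sided α = 0.05, power 90%, 2095 per group, about 4400 in total.

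**The plan's own figure.** The stated arcsine formula gives n = ½ × [(1.960 + 1.282) / (asin√0.10 − asin√0.072)]² = 2093.7, so 2094 per group. The stated 2095 is reproduced within rounding.

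**One planned effect on three scales.**
- Relative risk: 0.072/0.10 = 0.72
- Hazard ratio, assuming proportional hazards: ln(1 − 0.072)/ln(1 − 0.10) = 0.709
- Odds ratio: (0.072/0.928)/(0.10/0.90) = 0.698

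These do not contradict each other. They show only that the headline number depends on the route.

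**Does the choice of route affect the size of the trial?** Hardly. At 2095 per arm the expected events are 2095 × (0.10 + 0.072) ≈ 360. That gives 90.3% power for the log-rank test (Schoenfeld) and 89.9% for a comparison of two proportions.

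**How often do the routes disagree?** 20,000 trials per scenario were simulated with 2200 per arm. Assumptions: event times concentrated in the first days, uniform non-informative loss, all models unadjusted, and patients lost before day 14 without a stroke dropped from the logistic model. The article gives no loss-to-follow-up rate (its 5% is labelled medication nonadherence), so a range was used.

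| Scenario | Log-rank | Cox (Wald) | Logistic | Any of the three | Verdicts differ |
|---|---|---|---|---|---|
| Null, 0% loss | 4.9% | 4.7% | 4.8% | 5.0% | 0.4% |
| Null, 5% loss | 5.0% | 4.8% | 5.0% | 5.25% | 0.6% |
| Null, 10% loss | 5.0% | 4.9% | 5.0% | 5.4% | 0.8% |
| Planned effect, 5% loss | 91.1% | 90.9% | 91.0% | 91.4% | 0.9% |

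The simulation standard error at a 5% rejection rate is √(0.05 × 0.95/20,000) ≈ 0.15 percentage points. With 5% loss under the null, the log-rank and logistic z statistics correlate at 0.998.

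**If covariates are left open.** A separate simulation (4180 patients, 6000 trials per scenario, standard error about 0.3 points) took the better of an unadjusted test and a covariate-adjusted logistic test. Type I error rose from about 5% to 5.7–6.0%, assuming a covariate with standard deviation 0.6–0.9 on the log-odds scale. The documents give no basis for that strength. Choice among several covariate sets was not simulated.

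**Patients affected by early loss.** At an assumed 5% loss, about 4400 × 0.05 × (1 − 0.086) ≈ 201 patients have no known 14-day status, where 0.086 is the mean of the two planned risks. Leaving missing values missing most naturally means that these patients drop out of the logistic model.

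**The case against.** The strongest reply is that the Kaplan-Meier, Cox and log-rank sentence names the endpoint, the time window and the purpose, so it is the primary analysis. Logistic regression would then serve the binary secondary outcomes in Study outcomes, such as the dichotomised modified Rankin score. That may be what was meant, but the logistic sentence carries no such limit, and it is the one that speaks of significance. It is also fair that a condensed article may leave covariate lists and sensitivity analyses to an analysis plan not shown. The point here is narrower: two stated sentences compete.

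Several stronger readings are tempting, and the article does not support them.
- **Three competing tests.** The log-rank test is the Cox score test apart from ties, and the pair is conventional. There are two routes.
- **All models unadjusted.** The text is silent on adjustment. It does not exclude it.
- **Logistic regression loses every censored patient.** Those event-free at day 14 are known non-events and stay in. Only losses before day 14 are in question, and the article does not say that they are dropped. The conflict with intention to treat is possible, not stated.
- **Baseline data used only for balance testing.** Study outcomes also plans efficacy analyses stratified by etiologic subtype, time to randomisation, qualifying event and age.
- **Baseline tests used to select covariates.** No sentence says so. The tests tell us little in a randomised trial, but they decide nothing about efficacy.

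The time-to-event route is not free of the early-loss problem either. Visits are scheduled only at randomisation, day 14 and day 90, so censoring at the last visit, read literally, could place an early loss at day 0.

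**Conclusion.** The point holds as a conflict between two current sentences: the article does not fix which analysis decides the primary endpoint or which effect measure is reported. It is moderate and not a must-fix. With unadjusted models and non-informative loss the consequence is slight: type I error of about 5.25% at 5% loss for any-of-three testing, and disagreement in under 1% of trials. The 5.7–6.0% figure applies only if an adjusted logistic test is added to the choice after the data are seen, and it rests on an assumed covariate strength. It should not be read as the error rate of the plan as written. Informative loss could widen the gap, but the documents do not allow that to be quantified. The sample size is unaffected.

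**What to change.** Before unblinding, state the following.

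1. The primary analysis is a Cox model for time to first stroke within 14 days, adjusted for prespecified factors already collected: TIA versus minor stroke, age, and time from onset to randomisation. The treatment term in this model gives the deciding p-value. The log-rank test is supportive.
2. The Kaplan-Meier 14-day risk difference with 95% confidence interval is reported beside it, to match the percentage endpoint, as a supporting estimate that does not decide significance.
3. Logistic regression is a sensitivity analysis, with a rule for patients lost before day 14. The censoring time of such patients in the Cox model is stated too.
4. Baseline chi-square tests are not used to choose covariates. Descriptive baseline tables are enough.

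The cost is wording only. Prespecified adjustment may gain a little: simulated power moved from about 90% to 90–92% under the covariate strengths assumed above. The downsides are that the freedom to choose among tests is given up, and that the adjusted hazard ratio is a conditional measure, which is why the risk difference should be shown with it.

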### Study organization

The progress of the study would be monitored by the Data and Safety Monitoring Board (DSMB) to ensure the high standards of ethics and patient safety. The DSMB would monitor the trial via scheduled and unscheduled reviews, supervise stopping rules and unmasking, and maintain the confidentiality of internal discussions and validity of the reports.

An Executive Committee meeting would be organized to make major decisions. Quality control inspectors would be responsible for inspecting the quality of research sites and study data periodically, supervising any quality problem during the trial, and reporting to the Executive Committee. The members of the Steering Committee, including two project directors, would be members of the Executive Committee and would convene monthly (teleconferences or physical meetings) to review the status of the trial and available blinded data; they would take appropriate action regarding the conduct of the study.

An Adjudication Committee charter including membership, role, and responsibilities would be approved before the start of the trial by the Adjudication Committee and the Executive Committee. This committee would be composed of Academic Members, including an independent statistician, who were not otherwise participating in the trial.

